#### Adherence metrics

For participants allocated to iCT-PTSD-YP, we will report: (1) the number of times logged into the programme per week and in total; (2) time spent logged in per week and in total; (3) the number of modules completed in total and according to device used; (4) the number of therapist phone calls attended per week and in total, and the number of missed phone appointments; (5) time spent on phone calls per week and in total; (6) the number of messages to/from therapist per week and in total; (7) the number and proportion of young people who start treatment; (8) the number of weeks of therapy completed and (9) reasons for dropping out of treatment if known.

#### Acceptability outcomes

We will carry out qualitative interviews with young people, carers and therapists to gauge acceptability of iCT-PTSD-YP, and we will summarise interview data using content analysis. We will aim for these interviews to be representative of individuals involved in the feasibility trial (young people, carers, therapists), including young people who left the study or failed to adhere to the course of treatment, to provide a full range of views. We will interview trial participants in both arms about the acceptability of the research procedures including the assessment measures and their views on randomisation.

#### Primary clinical outcome

Presence of PTSD according to the Diagnostic and Statistical Manual of Mental Disorders (DSM-5) at 16 weeks post-randomisation, ascertained using the Clinician Administered PTSD Scale for DSM-5: Child and Adolescent version (CAPS-CA-5^30^), administered by trained reliable raters, blind to treatment allocation.

#### Secondary clinical outcomes

Child-reported outcomes at 16 weeks post randomisation: PTSD symptom severity (continuous score) on the CAPS-CA-5;^31^ PTSD symptom severity on the Child PTSD Symptom Scale for DSM-5 (CPSS-5^32^); PTSD symptom severity on the Children’s Revised Impact of Event Scale, 8-item version (CRIES-8^33 34^); and symptoms of depression and anxiety on the 25-item Revised Children’s Anxiety and Depression Scale (RCADS).^35^ Carer reported outcomes at 16 weeks post randomisation: Revised Children’s Anxiety and Depression Scale—parent version (RCADS-P^35^); and Strength and Difficulties Questionnaire—parent version (SDQ-P).^36^ At 38-week follow-up for participants in the iCT-PTSD-YP only, all secondary clinical outcomes apart from the CAPS-CA-5 will be repeated.

#### Process measures

The cognitive model^8^ on which treatment is based specifies a number of mechanisms of therapeutic change. We will test mediation via changes in appraisals, memory quality and ruminative thinking from baseline to mid-treatment (6 weeks post randomisation) using: the Child Post Traumatic Cognitions Inventory (CPTCI^37^); the Trauma Memory Quality Questionnaire (TMQQ^38^); and the Trauma Related Rumination Questionnaire items.^39^

#### Health economic outcomes

We will collect economic data on health utilities and resource use using the Child Health Utility Index 9D (CHU-9D)^40^ and the Child and Adolescent Service Use Schedule,^41^ administered at baseline and 16 weeks post-randomisation.

### Participant timeline

All participants will be assessed three times during the study: pre-treatment (week 0), mid-treatment (week 6 post-randomisation) and post-treatment (week 16 post-randomisation). Participants in iCT-PTSD-YP will complete a brief weekly measure of PTSD symptoms (CRIES-8) and mood (Likert scale) on the application, and a follow-up assessment (week 38 post randomisation). The first participant was randomised on 24 August 2020, and the last participant was randomised on 20 October 2021. The trial is currently closed to new recruitment.

### Sample size

We will recruit 17 participants per arm. In our previous RCTs of face-to-face CT-PTSD^11 12^ in young people, we had 4% drop-out, but we have conservatively allowed for approximately 20% drop-out, to give at least n=14 at post-treatment in each arm. An early-stage trial of this size will be sufficient to gather meaningful feasibility data on acceptability, compliance, retention and delivery. Power calculations are not typically used to determine sample size for feasibility studies. Therefore, we acknowledge an insufficient sample size to allow definitive between-group comparisons in this early stage RCT.^42 43^

### Recruitment

Participants will be recruited via three routes (see figure 1): (1) from school screening; (2) from NHS CAMHS teams; and (3) from primary care (GP or school referral) or self-referral. For all referral routes, consent will be sought before assessment, and eligibility will be determined by the clinical assessment.

**Figure 1 F1:**
[figure not shown]
Study flowchart. CAMHS, NHS Child and Adolescent Mental Health Services; CRIES-8, Children’s Revised Impact of Event Scale, 8-item version; GP, general practitioner.

### Allocation

Once a participant is confirmed as eligible and consenting to the study, they will be registered in the main participant database (held using the IBM-SPSS program). Participants will be randomised to receive iCT-PTSD-YP or WL at a 1:1 ratio. Randomisation will be carried out by the King’s College London CTU via a web-based service utilising minimisation with a random component. Minimisation factors will be sex and baseline PTSD symptom severity assessed by the CPSS (low:<51 and high:≥51). These factors were chosen in order to balance factors that may affect treatment response across the two arms. Other factors (such as age and trauma type) were not included due to the modest trial size.

### Blinding

All assessors of the primary and secondary clinical outcomes at follow-up at 16 weeks will be blind to trial arm allocation. Blind outcome assessors will be independent research assistants or clinical psychologists who are not part of the trial team. Assessors will be trained to standard on the CAPS-CA-5 interview, and inter-rater reliability will be assessed for 20 randomly selected interviews. The senior trial statistician (KG) will also be blind with all other members of the study team unblind to trial arm allocation. Unblinding of the senior trial statistician and the analysis of outcomes by intervention arm will occur after the initial draft of the statistical analysis report is generated.

### Data collection methods

For the primary clinical outcome, the CAPS-CA clinical interview is completed on the phone or via videoconference, with symptom level responses marked on the interview form and then entered into the trial database. For secondary clinical outcomes, questionnaires are completed online via a secure commercial system (Qualtrics) with responses downloaded to an electronic database and re-entered into the trial database. Feasibility outcomes are recorded by the study research assistant in the trial database. Adherence metrics are either recorded by the trial therapist in the study database or automatically captured by the application and downloaded to standard database software.

### Data management

Participant information will be kept confidential and managed in accordance with the Data Protection Act, General Data Protection Regulation (GDPR) policies, NHS Caldicott Guardian, The UK Policy Framework for Health and Social Care Research and Research Ethics Committee Approval. Personally identifiable data will be collected from participants including name and contact details. This information will be stored securely and separately from all other study-generated data, which will be anonymised. Each participant will be given a unique Participant Identification Number (PIN). All feasibility and clinical outcomes for the RCT will be stored in SPSS databases against the participant PIN. These databases will be stored on a secure King’s College London network drive, accessible to the study team only. Databases will be stored in a version control system, such that changes made over time can be examined and recovered. All databases will be registered in the King’s Data Protection Register.

### Statistical methods

A comprehensive statistical analysis plan (SAP) will be developed and agreed with the TSC before any analysis is carried out. The SAP will describe statistical procedures in detail. Quantitative analyses will employ up-to-date versions of statistical software (eg, Stata or R).

### Analysis of feasibility outcomes and adherence metrics

The feasibility outcomes and adherence metrics will be summarised with appropriate summary statistics (eg, means and SD/medians and IQRs for continuous outcomes; frequencies and proportions for count outcomes). Where appropriate some feasibility outcomes will either be reported only for the iCT-PTSD-YP arm or will be reported separately by arm.

### Clinical outcomes

As this is an early-stage trial designed to gather data on feasibility outcomes, it is not powered to detect between-arm differences: where between-arm differences are presented, they will be treated as exploratory and not treated as inferential. Data completeness will be summarised for clinical outcomes. All comparative analyses will primarily be conducted under the intention-to-treat (ITT) principle—all participants with a completed outcome will be included in the analysis and analysed according to the arm they were randomised to. Where deviations from ITT occur, this will be reported. We will carry out per-protocol analyses in addition to ITT, but these analyses will be treated as secondary to the ITT analysis. There will be no interim or subgroup analyses.

The primary and secondary clinical outcomes will be summarised with appropriate summary statistics by trial arm at each time point (primary, frequencies and proportions; secondary, means and SD). For each outcome we will estimate the treatment effect at 16 weeks, with the appropriate 95% CI. The iCT-PTSD-YP versus WL OR for remission from PTSD caseness at 16 weeks post-randomisation will be assessed using logistic regression with trial arm and the minimisation variables as covariates. The iCT-PTSD-YP versus WL mean differences in secondary clinical outcomes at 16 weeks post-randomisation will be estimated using linear regression, with trial arm, baseline outcome score and minimisation variables as covariates.

We will carry out per-protocol analyses for the primary outcome, and the CPSS-5 and CRIES-8 secondary outcomes at 16 weeks. These will be treated as secondary to the ITT analysis. The per-protocol analyses will be conducted in two populations. The first will consist of all participants with recorded outcome data who complete the minimum therapy needed to achieve clinical benefit (defined as completing at least the first six core modules (Psychoeducation about PTSD, Reclaiming life, Understanding PTSD, Developing a trauma narrative, Identifying hotspots, Updating the narrative)). The second per-protocol population will consist of all participants from the first per-protocol population who have additionally completed the core module, ‘Working with triggers’.

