### Interventions

#### iCT-PTSD-YP

iCT-PTSD-YP comprises therapist-supported online delivery of all components from our published manual of face-to-face CT-PTSD for young people.^27^ Treatment aims to change problematic appraisals, update trauma memories and change unhelpful coping responses. Treatment components are delivered in modules. There are 10 core modules for all young people (Psychoeducation about PTSD, Reclaiming life, Understanding PTSD, Developing a trauma narrative, Identifying hotspots, Updating the narrative, Working with triggers, Overcoming sense of danger, Visiting the site virtually and/or in person, Developing a blueprint) that are released to the young person sequentially by the therapist, and 11 optional modules which are released according to individual need (Relaxation, Sleep, Working with images, Working with physical difference, Anger, Grief, Shame, Guilt, Self-criticism, Rumination and Panic). Modules were co-designed with input from young people and built on the content of the modules developed for iCT-PTSD for adults.^28 29^ Modules are interactive (prompting for user action to progress through the application and requesting user text input and questionnaire responses) and include text, illustrations, audio case examples, animations and videos. Modules are intended for independent self-study by young people. Therapists can log onto the site to view young people’s progress including their text input and questionnaire responses. Young people and therapists can message each other via the application. Parents and carers are provided a separate log on to the carer version of the application. The carer version comprises eight modules, and the emphasis is on providing information to carers about therapy, including advice about how carers can help in young people’s recovery. Carers do not have access to any information that their child inputs to the application. Modules are delivered via a progressive web application on a smartphone or computer, hosted on a secure server. The application is not publicly available currently. For trial participants, an individual account requiring two-factor authentication log-in is created for the young person and their carer.

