#### WL

Young people will be placed on a WL and re-assessed 16 weeks after randomisation. Young people who require treatment at the end of the waiting period will be offered immediate iCT-PTSD-YP. WL control arms are commonly used in PTSD treatment trials^6^ because natural recovery from PTSD can be substantial.^30^ Use of a WL condition ensures that the effect of treatment is not overestimated, and shows whether treatment is impeding the rate of natural recovery.

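### Both per-protocol populations are defined by completing therapy modules, with no rule for the waiting-list arm, so the planned 16-week per-protocol contrast is either inestimable or compares selected completers with an unselected control arm

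*Protocol article*

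**What the plan says.** The Clinical outcomes section under Statistical methods commits to these analyses: "We will carry out per-protocol analyses for the primary outcome, and the CPSS-5 and CRIES-8 secondary outcomes at 16 weeks". The first population is set out as "The first will consist of all participants with recorded outcome data who complete the minimum therapy needed to achieve clinical benefit", and that minimum is "defined as completing at least the first six core modules", which are then named. The second is nested in the first: "The second per-protocol population will consist of all participants from the first per-protocol population who have additionally completed the core module" on working with triggers. Neither definition is limited to the iCT arm, and neither says how a WL participant enters.

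The WL section describes the control arm: "Young people will be placed on a WL and re-assessed 16 weeks after randomisation". Access to the intervention comes afterwards: "Young people who require treatment at the end of the waiting period will be offered immediate iCT-PTSD-YP". The iCT-PTSD-YP section says that the therapist releases the core modules in sequence, and of access outside the trial it says: "The application is not publicly available currently".

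The only 16-week effect measures specified are between-arm ones. The odds ratio for remission "will be assessed using logistic regression with trial arm and the minimisation variables as covariates", and the continuous outcomes use linear regression with trial arm, baseline score and the minimisation variables. The same section ranks per-protocol below ITT and labels between-arm differences exploratory.

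**The concern.** A per-protocol population needs a definition of adherence for each arm being compared. Here adherence is defined only by something that one arm receives and the other cannot receive before the endpoint. The analyst is left with a set that has no controls, or must supply a rule that the protocol does not contain.

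The obvious rule is to keep every WL participant with an outcome. That restores a control group but gives up the balance that randomisation provided: the iCT side is filtered on behaviour during treatment and the WL side is not. The resulting difference mixes the effect of therapy with whatever distinguishes completers from non-completers.

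The Introduction says the data will inform the design and size of a larger trial. A per-protocol odds ratio or mean difference could be taken forward as the effect of an adequate dose of therapy, which neither version estimates.

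**Working it through.** **Inputs from the protocol.** 17 participants per arm; about 20% drop-out allowed; at least 14 per arm at post-treatment (Sample size). Model terms: trial arm and two minimisation variables, sex and baseline severity (Clinical outcomes; Allocation).

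**The plan's own figure.** 17 × (1 − 0.20) = 13.6, which rounds to 14. Conversely, 14 of 17 is 17.6% drop-out. The stated figure reproduces.

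**Step 1: the definitions as written.** A WL participant who follows the protocol has completed 0 modules at week 16. WL members of the first set: 0 of about 14. The second set is a subset of the first, so also 0. Every member of either set is then in the iCT arm, and the arm indicator equals the intercept. The logistic design matrix has 4 columns (intercept, arm, sex, severity) but rank 3, whether the iCT side holds 14, 11 or 8 people (100%, 80% or 60% completion, assumed). The arm odds ratio cannot be estimated. The same collinearity removes the CPSS-5 and CRIES-8 mean differences.

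**Step 2: the module rule for iCT only, all WL kept.** The model can now be fitted. To see what it returns when therapy does nothing, assume (none of this is in the protocol) 25% remission in both arms, 70% of the iCT arm completing, and completers differing from non-completers in their odds of natural remission by a factor r. Write pc and pn for the remission risks of completers and non-completers. Solve

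0.70 × pc + 0.30 × pn = 0.25, with pc/(1 − pc) = r × pn/(1 − pn).

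| r | pc | pn | Spurious risk difference, pc − 0.25 | Spurious OR |
|---|---|---|---|---|
| 1 | 0.250 | 0.250 | 0 | 1.00 |
| 1.5 | 0.272 | 0.199 | +0.022 | 1.12 |
| 2 | 0.286 | 0.167 | +0.036 | 1.20 |
| 3 | 0.303 | 0.126 | +0.053 | 1.30 |
| 1/1.5 | 0.226 | 0.305 | −0.024 | 0.88 |
| 1/3 | 0.184 | 0.404 | −0.066 | 0.68 |

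The last two rows cover the case in which early improvers stop using the modules. Over a wider assumed grid (remission 20% to 40%, completion 60% to 80%, completers 1.5 to 3 times as likely to remit as non-completers), the odds ratio with no true effect runs from 1.09 to 1.80. It is 1.00 only when completion is unrelated to prognosis.

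**Step 3: the bias against the precision.** With 14 WL participants, 0.70 × 14 ≈ 10 completers and 25% remission in both groups, SE = √[0.25 × 0.75 × (1/14 + 1/10)] = 0.179. The 95% half-width is 1.96 × 0.179 = 0.35. A bias of 2 to 5 points is small beside 35.

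**Step 4: what a complier average causal effect (CACE) would and would not secure.** With one-sided access, CACE = ITT risk difference / completion share. For an illustrative ITT difference of 0.35 and 70% completion, 0.35/0.70 = 0.50. This assumes that iCT participants below the threshold gain nothing. If they gained 0.20, the completer effect would be (0.35 − 0.30 × 0.20)/0.70 = 0.41, so the CACE would overstate it by about 9 points. Some gain is plausible, since these participants may still work through some modules and are to have at least weekly therapist contact. At the seven-module threshold the assumption conflicts with the protocol itself: someone with exactly the first six modules has already reached what the protocol calls the minimum for benefit.

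**The case against.** The strongest reply is that a rule about completing therapy naturally applies to the arm offered therapy, that a WL participant who waits has followed the protocol, and that the analysis plan, which is not shown, can say so in one line. No statistician would fit an arm effect in a one-arm dataset. What remains is the familiar weakness of any per-protocol analysis, which the protocol meets by ranking it below ITT. The bias figures rest on assumed inputs and are swamped by sampling error.

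Much of this stands. The empty control set is what the words produce, not what the authors probably intended. Size and direction of the bias are unknown, and adjustment for baseline severity may remove part of it. The reply does not dispose of the point, however. The protocol does not leave these populations to the analysis plan: it fixes them, down to named modules, and words them as covering all participants. Supplying the missing line still leaves adherence-selected completers facing an unselected arm.

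A reader might go further and infer that WL participants who take iCT after week 16 and finish six modules would count, which would select WL on the outcome and force its remission rate to about zero. The documents do not support that. Nothing suggests that a week-16 outcome would be classified by later module use, and needing treatment at the end of the wait is not defined as meeting PTSD criteria on the CAPS-CA-5. Nor can one infer that the comparison must favour iCT, since that requires completers to have the better natural prognosis.

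**Conclusion.** The point holds, at minor to moderate severity. That no protocol-adherent WL participant can meet either definition by week 16 follows from the text alone, as does the resulting inestimability. That the natural repair compares non-equivalent groups also needs no assumption about numbers; only the magnitude does. At 25% remission, 70% completion and completer odds ratios of 1.5 to 3, the spurious difference is about +2 to +5 points, and the sign flips if those odds ratios are inverted.

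It would be too strong to conclude that the trial's efficacy analysis lacks a control group. The ITT analysis keeps both arms and is unaffected, the study's primary outcomes are feasibility, adherence and acceptability, and no decision rule in the protocol depends on a per-protocol result. It would also be too strong to read the protocol's phrase about minimum therapy as establishing that less therapy has no effect. That remains an assumption at six modules, and the phrase contradicts it at seven.

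**What to change.** Amend the Clinical outcomes section, and carry the wording into the analysis plan before any analysis by arm:

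- State that the module criteria apply to the iCT arm only, and report PTSD diagnosis, CPSS-5 and CRIES-8 in both completer sets as descriptive iCT-only data without a between-arm contrast.
- If a between-arm adherence-adjusted estimate is wanted, specify an exploratory CACE at the six-module threshold only. Use randomised arm as the instrument, count modules completed before the week-16 assessment as treatment received, keep all randomised participants with outcomes in both arms, and adjust for baseline.
- State the exclusion restriction as an assumption, and show the estimate over a range of assumed gains in participants below the threshold.
- Do not use this estimator for the seven-module set.

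The cost is a few sentences and a few lines of code, with no new data. The drawback is a very wide confidence interval with about 14 per arm, so the CACE would be a supplement to ITT and not a planning value on its own.

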### Process outcomes

An exploratory mediation analysis will be carried out to assess the indirect effect of treatment allocation on the primary clinical endpoint via the CPTCI, the TMQQ and items relating to rumination, measured at 6 weeks post-randomisation. The total, direct and indirect effects of treatment allocation on 16-week PTSD caseness will be estimated using the Stata paramed command^44 45^ to properly calculate effects for a binary outcome, along with associated 95% CIs. CIs for the indirect effect will be estimated using the percentile bootstrap.^46^

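### The mediation plan claims proper effects on PTSD caseness, but with a logistic outcome model the closed-form odds ratios need a rare outcome, and bootstrap limits may be unstable at 14 per arm

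*Protocol article*

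**What the plan says.** The Process outcomes section of the protocol article plans an exploratory mediation analysis of 16-week PTSD caseness. The mediators are the CPTCI, the TMQQ and the rumination items at week 6. Total, direct and indirect effects come from Stata paramed, chosen "to properly calculate effects for a binary outcome, along with associated 95% CIs". For the interval, "CIs for the indirect effect will be estimated using the percentile bootstrap".

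The section does not name the outcome model (logistic or log-linear), the covariates, any arm-by-mediator interaction, or the handling of resamples that fail to converge. The Clinical outcomes section analyses the same endpoint by logistic regression on arm and the two minimisation variables and reports an odds ratio.

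The Process measures section describes mediation via "changes in appraisals, memory quality and ruminative thinking from baseline to mid-treatment (6 weeks post randomisation". Table 1 shows all three mediators collected at baseline and week 6.

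On size: "We will recruit 17 participants per arm", and the drop-out allowance is meant "to give at least n=14 at post-treatment in each arm".

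**The concern.** Under a logistic outcome model and a linear mediator model, the closed-form natural-effect odds ratios approximate the true ones only when the outcome is rare. The eligibility criteria require PTSD as the main presenting problem, so caseness starts near 100%. The article gives no 16-week rate and says that natural recovery can be substantial. Even so, caseness is very unlikely to be rare in the waiting-list arm. Counting remission as the event does not help, because remission would then have to be rare in both arms, which would mean that treatment barely works.

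There is a second, separate risk. With about 28 people, some bootstrap resamples will be separated, so that a logistic coefficient has no finite estimate. A 95% percentile limit is set by the outer 2.5% of resamples on each side, so a few divergent fits on one side can determine it.

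The abstract says this analysis will consider which mechanisms mediate recovery. At stake are the size of the reported effects and the credibility of their intervals.

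**Working it through.** **Sample size.** The Sample size section gives 17 per arm and says "we have conservatively allowed for approximately 20% drop-out". 17 x 0.80 = 13.6, which rounds to 14, so the stated minimum of 14 per arm (28 in total) reproduces.

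**Assumptions (none of these figures is in the article).** Logistic outcome model without interaction; normal mediator with SD 1; arm effect on the mediator a = -0.8 SD; mediator log-OR t2 of 0.5, 1 or 2 per SD; waiting-list (WL) caseness 80% or 60%; iCT caseness 30%.

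**Formulas.** With t1 the arm log-OR given the mediator:
- closed form: indirect OR = exp(t2 x a); total OR = exp(t1 + t2 x a)
- exact: average the logistic risk over the mediator distribution under each arm by numerical integration, then form the odds ratios
- log-scale proportion mediated = ln(indirect OR) / ln(total OR)

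Closed-form indirect ORs: exp(-0.4) = 0.670; exp(-0.8) = 0.449; exp(-1.6) = 0.202.

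Exact total ORs follow from the assumed rates. For 80% against 30%: (0.3/0.7)/(0.8/0.2) = 0.107. For 60% against 30%: (0.3/0.7)/(0.6/0.4) = 0.286.

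| WL / iCT caseness | t2 | Indirect OR: formula / exact | Total OR: formula / exact | Proportion mediated: formula / exact |
|---|---|---|---|---|
| 80% / 30% | 0.5 | 0.670 / 0.684 | 0.095 / 0.107 | 0.17 / 0.17 |
| 80% / 30% | 1 | 0.449 / 0.513 | 0.069 / 0.107 | 0.30 / 0.30 |
| 80% / 30% | 2 | 0.202 / 0.376 | 0.027 / 0.107 | 0.44 / 0.44 |
| 60% / 30% | 0.5 | 0.670 / 0.684 | 0.266 / 0.286 | 0.30 / 0.30 |
| 60% / 30% | 1 | 0.449 / 0.513 | 0.221 / 0.286 | 0.53 / 0.53 |
| 60% / 30% | 2 | 0.202 / 0.376 | 0.128 / 0.286 | 0.78 / 0.78 |

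As a control, at 2% against 0.5% caseness and t2 = 1 the formula gives 0.449 against an exact 0.454. The discrepancy in the table therefore comes from the outcome being common.

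With WL caseness 80%, t1 = -1.0 and t2 = 1.2, the indirect OR is 0.38 by formula against 0.47 exact, and the total OR 0.14 against 0.21.

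**Separation.** The interval in question is for the indirect effect, which depends on the mediator coefficient. What matters is separation that reaches that coefficient. If every waiting-list participant in a resample is a case, the arm coefficient diverges but the mediator coefficient can stay finite. At 14 per arm and 70-80% WL caseness, simulated shares of resamples in which the mediator coefficient is affected are:
- arm and mediator only: about 1-8%
- with two binary covariates, such as the minimisation variables: about 7-25%

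A separate run with arm and mediator only (WL caseness 80%, t2 = 1.2 and 1.5) shows the difference between the two counts. Any separation occurred in 14% and 18% of resamples, and separation of the mediator coefficient in 4% and 10%. In 31% and 65% of data sets, more than 2.5% of resamples had a separated mediator coefficient. At 17 per arm the resample shares fell to 2% and 4%. Monte Carlo error is several percentage points.

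**The case against.** **The outcome model is not stated.** This stands. Logistic is inferred from the Clinical outcomes section, and a log-linear model would escape the rare-outcome objection. A reader might infer that the effects as planned are overstated without condition; the article does not support that. The choice of link, covariates and handling of failed fits may also sit in the statistical analysis plan, which is not shown, so their absence is no fault. What the article does fix is a binary outcome, the software, the interval method and the claim that the result is proper.

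**The error depends on the mediator.** This stands too. For a weak mediator the indirect effect is almost unchanged, and the proportion mediated hardly moves in any row of the table. The claim about which mechanisms mediate recovery is harmed less than the odds ratios alone suggest.

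**Separation can be overcounted.** A reader might infer that 20% to 50% of resamples spoil the interval. That counts any separation, and the upper figure needs an arm-by-mediator interaction that the article never mentions. The shares that reach the mediator coefficient are lower.

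**The two process sections can be read together.** A reader might see a contradiction between change from baseline and a mediator measured at week 6, and conclude that baseline appraisals or rumination confound the result. A week-6 mediator adjusted for its baseline is a standard way to study change. Process outcomes lists no covariates at all, and silence is not exclusion.

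**The analysis is exploratory.** Of between-arm differences the Clinical outcomes section says "they will be treated as exploratory and not treated as inferential", and the Sample size section notes "Power calculations are not typically used to determine sample size for feasibility studies". This lowers the weight of the point, but it does not make an approximation valid outside its range.

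**Conclusion.** The point holds in a conditional and modest form. Caseness will be common, so if the outcome model is logistic, closed-form effects cannot be called properly calculated. Under the assumed values the error in the indirect odds ratio runs from negligible (0.67 against 0.68-0.69) through moderate (0.45 against about 0.51) to large (0.20 against 0.37-0.38) as the mediator log-OR rises from 0.5 to 1 to 2. The log-scale proportion mediated is nearly unaffected. Percentile limits for the indirect effect may be unstable at 14 per arm, chiefly when covariates are included.

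The logistic link, the 16-week rates, the -0.8 SD mediator effect and the mediator log-ORs are all assumptions. That caseness is not rare is an inference from eligibility, though a strong one. The article does not support a claim of contradiction between the two process sections, or of uncontrolled confounding by baseline mediators.

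**What to change.** 1. Keep 16-week caseness as the mediation outcome, since diagnosis is the primary clinical outcome. State the outcome model and compute natural effects without the rare-outcome approximation, for example as risk differences by standardisation from a Firth-penalised logistic model.
2. Adjust mediator and outcome models for the baseline value of the mediator, already collected, so that Process outcomes visibly matches the change from baseline in Process measures.
3. Keep the percentile bootstrap, and report the share of resamples that are separated.
4. Add week-16 CAPS-CA-5 severity, analysed with linear models, as a supporting mediation analysis. It avoids both the rare-outcome condition and separation.
5. Delete the word properly.

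No new data are needed. The cost is a change of wording and slightly more analysis work, for an analysis that remains exploratory.
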